#### Standard Care Control Group

Participants in the control group will receive standard care and therefore will not receive the home nebulizer. The spirometer, pulse oximeter, and smart inhalers will be provided but only used for observational monitoring in the control group, similar to the investigational devices (cough monitor, air quality sensor, and sleep monitor). The control group will be able to use the Engage portal to share measurements and questionnaire data, but they will not receive any feedback or data interpretation. This same protocol holds for the 3-month follow-up period to be able to assess differences in the primary and secondary outcome parameters after cessation of the intervention.

### Outcome Measures

Demographic characteristics (age, gender, medication use, other medication use, allergy due to aeroallergens, eczema, doing sports, and smoking behavior at home) will be retrieved from electronic patient records.

The primary outcome variables are health care utilization and costs. All health care activities (ie, hospital admissions, outpatient visits, emergency visits, diagnostic activities, etc) will be labeled using the Dutch health care registration system of the Dutch Healthcare Authority. The accompanying health care costs will be calculated using activity-based costing [50]. Furthermore, the specific eHealth care costs will be calculated using bottom-up gross costing, consisting, for example, of the working hours of the HCPs and the depreciation costs of the monitoring devices [50].

Multimedia Appendix 1 contains the description and analysis of other outcome variables to investigate the effects of the eHealth intervention, which will enable research that can further improve pediatric eHealth asthma care.

All data will be handled according to the EU GDPR and the Dutch Act on the Implementation of the GDPR and securely stored in the Castor EDC system.

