### Sample Size

Previous data from an eHealth clinical feasibility study (N=30) using a comparable intervention within the same patient population revealed a reduction in health care utilization of 80% [34]. This data showed an average reduction in the number of outpatient consultations from 3.9 to 0.7 (SD 1.8) per patient per half year.

A power simulation was performed for a Mann-Whitney-Wilcoxon 2-sided test. The health care utilization was assumed to be Poisson distributed with means according to the clinical feasibility study. For the control group, the Poisson rate was equated to the historical data of the pilot divided by 2 to account for the study durations. The intervention group’s rate was taken to be the postdata of the feasibility study divided by 2. As the ALPACA study makes use of the intention-to-treat principle, noncompliance to the intervention was included in the simulation. The number of nonadherent participants was random in the simulation according to a binomial distribution (similar to the clinical feasibility study data, with 3 out of 33 participants). This was used to calculate the control group rate, which is a conservative estimate of no benefit from the intervention. Together with the assumption of an Alpha Type 1 error of 0.05, the sample size calculation results in 36 (18 intervention and 18 controls), with a power of 97.1% for the primary outcome and 80% for secondary follow-up effects (assuming a lasting effect of 80%). Accounting for dropouts (n=4), we would need to include 40 children.

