### Data and Statistical Analyses

Descriptive statistics will be used to examine all continuous outcome measures expressed in mean and SD for normally distributed variables and with median and IQR for nonnormal distributed variables. Univariate analyses will be performed with SPSS software (version 22.0; IBM Corp). The homogeneity of variances will be verified with the Levene test. Histogram plots and the Shapiro-Wilk test will be used to determine whether the variables are normally distributed among the groups. A *t* test (or nonparametric Mann-Whitney U test) will be used to compare the primary outcomes between eHealth care and standard care, and *P≤*.05 will be considered significant. The analysis will be performed according to the intention-to-treat principle [51], and missing data will be handled with pairwise deletion. An interim analysis will be conducted after half the participants are done with the intervention. In case the interim analysis reveals a significant increase in health care utilization in the intervention group, this study will be prematurely ended.

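### Utilization and costs are both primary with no rule joining them, so the error rate of the primary claim is undefined and the stated power covers visit counts only

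*Protocol article*

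**What the plan says.** The Outcome Measures section of the protocol article states: "The primary outcome variables are health care utilization and costs". It ranks neither above the other. Only the other outcome variables are sent to Multimedia Appendix 1, which is listed as covering the secondary parameters.

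The Data and Statistical Analyses section says that a t test or a Mann-Whitney U test "will be used to compare the primary outcomes between eHealth care and standard care", with P≤.05 as the threshold. The plural matches the Outcome Measures section. No hierarchy, alpha split or joint criterion is given.

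The Sample Size section works with one outcome. "A power simulation was performed for a Mann-Whitney-Wilcoxon 2-sided test", under the "assumption of an Alpha Type 1 error of 0.05", and "The health care utilization was assumed to be Poisson distributed with means according to the clinical feasibility study". The means come from an "average reduction in the number of outpatient consultations from 3.9 to 0.7 (SD 1.8) per patient per half year". The result is 18 per group "with a power of 97.1% for the primary outcome and 80% for secondary follow-up effects". No mean, SD or effect for costs appears.

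The Objectives and Hypothesis sections join utilization and costs with the word 'and', but neither says that both must be significant for the trial to succeed.

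**The concern.** With two primary outcomes, a plan has to say which combinations of results count as success. This one does not, and the two obvious readings have different consequences. If either outcome suffices, two unadjusted tests at 0.05 give more than a 5% chance of at least one false positive primary result. If both are needed, the type I error is held, but the power of the primary claim is unknown because only the counts were simulated.

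A split result is realistic. Costs are built partly from the recorded care activities, but the Outcome Measures section also costs the eHealth care itself, giving staff hours and device depreciation as examples. Visits could fall while total cost does not. The protocol has no rule for reading that result, although the Discussion expects policy makers to use the findings.

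**Working it through.** **1. Reproduce the stated power.** All inputs are from the Sample Size section.
- Control rate: 3.9 / 2 = 1.95 visits per 3 months.
- Intervention rate: 0.7 / 2 = 0.35 visits per 3 months.
- Non-adherent intervention patients: binomial with probability 3/33 = 9.1%, given the control rate.
- 18 per group, two-sided Mann-Whitney test, alpha 0.05.

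A simulation of 20,000 trials gives a power of 96.8% with continuity correction and 97.1% without. The article states 97.1%. The figure reproduces, for counts at an unsplit 0.05.

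**2. Error if either outcome suffices.** Treat the two test statistics Z1 and Z2 as bivariate normal with correlation ρ, both null hypotheses true.
- Two-sided familywise error = 1 − P(|Z1| < 1.96, |Z2| < 1.96).
- At least one false reduction = 1 − P(Z1 > −1.96, Z2 > −1.96).

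For ρ = 0 these are 1 − 0.95² = 9.75% and 1 − 0.975² = 4.9%. The documents give no correlation between utilization and costs, so a range is shown.

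| Assumed ρ | At least one false positive, either direction | At least one false reduction |
|---|---|---|
| 0 | 9.75% | 4.9% |
| 0.3 | 9.5% | 4.8% |
| 0.5 | 9.1% | 4.5% |
| 0.7 | 8.3% | 4.2% |
| 0.9 | 7.0% | 3.5% |
| 0.95 | 6.5% | 3.2% |
| Nominal, one test | 5% | 2.5% |

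Both columns fall toward the nominal level as ρ nears 1.

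**3. Check at the trial's size.** Null trials of 18 versus 18 were simulated with Poisson counts (mean 1.95) and with cost as a sum of lognormal unit costs. The unit-cost distribution is an assumption. Count-cost correlations were about 0.6, 0.5 and 0.3, and the chance of at least one P≤.05 was 7.4%, 8.3% and 8.6%. Each single test ran slightly below 5% (4.6% to 4.8%), so these figures sit a little under the normal approximation.

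**4. Error and power if both are required.** A false joint claim needs at least one true null hypothesis to be rejected at 0.05, so the error is at most 5%. Joint power cannot exceed the power for counts, about 97%. How far below it lies depends on a cost effect and a cost variance that the article does not give.

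**5. Price of each repair for utilization, at 18 per group.**
- Fixed sequence, utilization first at 0.05: power about 97%, familywise error 5%.
- Split of 0.025 each: simulated power 94.2% to 94.4%, familywise error at most 5%.

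**6. The interim look.** The Data and Statistical Analyses section stops the trial only for a significant increase in utilization. It does not add to false claims of benefit and is left out of these figures.

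**The case against.** A reader might infer that the trial runs a 7% to 10% false-claim rate in place of 5%. The documents do not support that as a flat statement. It holds only if either outcome alone carries the claim, which no section says, and only if both null hypotheses are true. It also counts errors in both directions, whereas the Hypothesis section expects a reduction. The chance of a false reduction stays below 5%, although above the 2.5% that one two-sided test would allow. If utilization truly falls, one null hypothesis remains and its error is 5%. If the eHealth costs are added to the intervention group's total, which is not said explicitly, a false cost reduction is less likely than the symmetric model assumes. All of this stands and limits the size of the point.

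A reader might also infer that the 97.1% is wrong. It is not. The Sample Size section says what was simulated, and the figure reproduces. It misleads only if read as the power of a joint utilization-and-cost claim.

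A third reading, that utilization leads and costs accompany it, fits the singular outcome in the Sample Size section and an interim rule based on utilization alone. It is plausible, but the Outcome Measures section does not say it.

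Finally, multiplicity rules are often left to an analysis plan, and this is a condensed article. That has some force. Yet the article itself fixes the two primary outcomes, the test and the threshold, and sends only the other outcomes to the appendix. The flaw is in stated rules that do not fit together, beyond any omitted detail.

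**Conclusion.** The point holds in conditional form. Followed as written, the plan has two unadjusted primary tests and a single power figure for one of them.

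- **Either outcome suffices, both null hypotheses true:** two-sided familywise error of about 7.0% to 9.75%, and a false-reduction error of about 3.5% to 4.9% against a nominal 2.5%. This rests on assumed correlations of 0.9 down to 0 and a bivariate normal model.
- **Both must be significant:** the error is controlled, but 97.1% is not the power of the claim, and the joint power cannot be computed from the article.

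The trial remains viable at its planned size. The decision rule should be fixed before the data are analysed.

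**What to change.** In the Outcome Measures and Data and Statistical Analyses sections, make utilization the first primary test at two-sided 0.05, and test costs at 0.05 only if utilization is significant. Report the mean cost difference with its confidence interval whatever the utilization result. In the Sample Size section, state that 97.1% refers to utilization counts only and rests on outpatient consultation rates. Because utilization in the Outcome Measures section also includes admissions, emergency visits and diagnostic activities, say which count enters the first test.

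The cost is about one sentence in each section. A formal cost claim becomes conditional on utilization, which matters because costs are half of the main objective. Utilization power stays at about 97% with no added patients. If the sponsor wants costs to be claimable independently, a 0.025 split also controls the error and leaves about 94% power for utilization.

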### Sample Size

Previous data from an eHealth clinical feasibility study (N=30) using a comparable intervention within the same patient population revealed a reduction in health care utilization of 80% [34]. This data showed an average reduction in the number of outpatient consultations from 3.9 to 0.7 (SD 1.8) per patient per half year.

A power simulation was performed for a Mann-Whitney-Wilcoxon 2-sided test. The health care utilization was assumed to be Poisson distributed with means according to the clinical feasibility study. For the control group, the Poisson rate was equated to the historical data of the pilot divided by 2 to account for the study durations. The intervention group’s rate was taken to be the postdata of the feasibility study divided by 2. As the ALPACA study makes use of the intention-to-treat principle, noncompliance to the intervention was included in the simulation. The number of nonadherent participants was random in the simulation according to a binomial distribution (similar to the clinical feasibility study data, with 3 out of 33 participants). This was used to calculate the control group rate, which is a conservative estimate of no benefit from the intervention. Together with the assumption of an Alpha Type 1 error of 0.05, the sample size calculation results in 36 (18 intervention and 18 controls), with a power of 97.1% for the primary outcome and 80% for secondary follow-up effects (assuming a lasting effect of 80%). Accounting for dropouts (n=4), we would need to include 40 children.

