### Strengths and Limitations

This study is a follow-up of a quasi-experimental eHealth evaluation study [34]. Therefore, the involved HCPs of the hospital are experienced with using eHealth technology, and the care pathway is already aligned to deliver remote care in a safe and efficient way, which are commonly the most important barriers to successful eHealth evaluation trials [52]. Moreover, improvements based on prior eHealth trials within our hospital are integrated into this protocol to maximize its feasibility.

Another strength of the ALPACA study is the fact that it uses a set of home-monitoring devices chosen to be as unobtrusive as possible to minimize the daily living burden of the participating children and their parents. The current literature shows an increase in the development and evaluation of these unobtrusive sensing systems, enabling adherent long-term use for monitoring chronic disease course and management [53]. Additionally, this study uses a communication platform to provide children and their parents the opportunity to unobtrusively share a request for help or advice and integrate time- and event-based repeated home monitoring measurements or diary entries to obtain valid, real-life self-reports [42].

Objectified feedback to participants in eHealth care about inhalation technique (via videos) and therapy adherence (via smart inhaler data) could be a great addition to the current asthma care for children [54], as inhalation technique and therapy adherence appear to be poor but often remain “the elephant in the room” and stay unaddressed [55-58]. Automated synchronization of the mobile device and the inhaler add-ons provides a burden-free way to increase awareness of therapy adherence among children with asthma and their parents and provides HCPs with the necessary information to make informed medication adjustments [34,59].

Since a critical evaluation of financial cost-effectiveness is lacking in the literature for electronic health tools in pediatric asthma [60], the design of the ALPACA study is favored, as all direct hospital health care utilization is registered in combination with asthma outcomes. This gives us the opportunity to perform a thorough cost analysis of the care transformation to eHealth care. Moreover, the follow-up period of this study allows us to investigate whether the effect may endure when eHealth is ceased, providing interesting information on the possible long-term benefits of eHealth care.

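### The 97.1% power stated for the primary outcome covers outpatient consultation counts only; none is stated or derivable for total utilization or costs, and the follow-up figure is sensitive to the Poisson assumption

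*Protocol article*

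**What the plan says.** All references are to the protocol article.

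- **Outcome Measures:** "The primary outcome variables are health care utilization and costs". Utilization includes admissions, outpatient visits, emergency visits and diagnostic activities. Costs include the specific costs of eHealth care, such as staff hours and device depreciation. Table 1 also lists telephone and internet consultations under utilization data.
- **Sample Size, inputs:** the only rates given are an "average reduction in the number of outpatient consultations from 3.9 to 0.7 (SD 1.8) per patient per half year", from a feasibility study. On the rates used, "For the control group, the Poisson rate was equated to the historical data of the pilot divided by 2", and the intervention rate is half of the pilot's post value. On the distribution, the section states: "The health care utilization was assumed to be Poisson distributed with means according to the clinical feasibility study". Nonadherence is binomial at 3 of 33, with nonadherent children at the control rate.
- **Sample Size, test and result:** "A power simulation was performed for a Mann-Whitney-Wilcoxon 2-sided test", with alpha 0.05 and 18 children per arm. The result is then given once for each period: "with a power of 97.1% for the primary outcome and 80% for secondary follow-up effects (assuming a lasting effect of 80" percent). Four dropouts bring the total to 40.
- **Strengths and Limitations**, on the earlier study: "This study is a follow-up of a quasi-experimental eHealth evaluation study [34"].
- **Randomization and Blinding:** allocation is stratified on asthma hospital visits in the past 6 months, in four strata from 0-1 to 6 or more. The reason given is that earlier exacerbations and utilization are risk factors for later exacerbations.

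**The concern.** The label on the power figure is wider than the calculation behind it. Outpatient consultations are one item within utilization, and costs do not enter the calculation at all. The intervention itself adds internet contacts and eHealth costs, so the pilot's fall in outpatient visits cannot simply be carried over to total utilization or to costs.

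Two planning assumptions also favour a high figure:

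- **Control rate.** It is a before-period rate, so the whole before-after fall is credited to eHealth. Some children enter because of a recent exacerbation or uncontrolled asthma (Table 2), so a concurrent control arm may improve somewhat without the intervention.
- **Common rate.** A single Poisson rate gives every control child the same expected number of visits. In that model a child's past count carries no information about future counts, whereas the reason given for stratifying assumes that it does.

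The Hypothesis section expects significant reductions in both utilization and costs, and the article offers the results to policy makers. If the 97.1% is taken at its label, a null cost result would be read as evidence against an effect from a well-powered comparison. The same applies to follow-up, where the stated power is only 80% to begin with.

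**Working it through.** **Inputs from Sample Size**

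- Control mean per 3 months: 3.9 / 2 = 1.95.
- Intervention mean per 3 months: 0.7 / 2 = 0.35. The relative reduction is (3.9 − 0.7) / 3.9 = 82%.
- Each intervention child is nonadherent with probability 3/33 = 9.1%, and then has mean 1.95.
- 18 per arm, two-sided Mann-Whitney test, alpha 0.05.
- Follow-up with 80% of the effect lasting, read as a mean of 1.95 − 0.8 × (1.95 − 0.35) = 0.67.

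**Step 1. Reproduce the stated figures** (simulation, 40,000 trials per scenario, normal approximation with tie correction)

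| Period | Stated | Reproduced |
|---|---|---|
| Intervention | 97.1% | 97.0% with, 97.1% without continuity correction |
| Follow-up | 80% | about 82% |

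The article does not give the exact follow-up model. A second reading, in which 80% of adherent children keep the 0.35 rate, gives 82-83%. The match for the intervention period shows that outpatient rates alone are enough to produce 97.1%.

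**Step 2. Compare the scope**

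| Primary outcome as defined | Input to the power calculation |
|---|---|
| Utilization: outpatient visits | 3.9 and 0.7 per half year |
| Utilization: admissions, emergency visits, diagnostics, telephone/internet contacts | none |
| Costs, including eHealth costs | no mean, SD or effect |

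Power for the second and third rows cannot be computed from the article.

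**Step 3. Check what the SD of 1.8 can show**

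The text does not say which quantity it belongs to. The corresponding Poisson SDs are:

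- post count: √0.7 = 0.84
- before count: √3.9 = 1.97
- change, if the two counts are independent: √(3.9 + 0.7) = 2.14

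Only the first reading would indicate overdispersion (1.8² / 0.7 = 4.6).

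**Step 4. Sensitivity, one departure at a time, 18 per arm**

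The dispersion values, lower control rates and smaller reduction are assumptions; the article gives none. Negative binomial variance is μ + μ²/k. For control children (μ = 1.95), k=5 gives an SD of √(1.95 + 0.76) = 1.65, k=2 gives √(1.95 + 1.90) = 1.96, and k=1 gives √(1.95 + 3.80) = 2.40. The Poisson SD is √1.95 = 1.40.

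| Intervention period | Power |
|---|---|
| Stated assumptions | 97% |
| Stated means, k = 5 / 2 / 1 | about 93% / 86% / 73% |
| Poisson, control rate 1.5 / 1.2, intervention 0.35 | about 87% / 70% |
| Poisson, control 1.95, true reduction 50% | about 54% |

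| Follow-up (mean 0.67) | Power |
|---|---|
| Poisson, 18 per arm | about 82% |
| Poisson, 20 per arm (all 40 stay) | about 86% |
| k = 5 / 2 / 1, 18 per arm | about 71% / 58% / 42% |

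**The case against.** The strongest reply is that this is conditional power with its conditions disclosed. The section names outpatient consultations, the Poisson model, the pilot rates and the nonadherence allowance, and the arithmetic is right. It speaks of the primary outcome in the singular and never mentions power for costs. That is fair as to the arithmetic, but it does not repair the label: Outcome Measures names two primary outcomes and defines utilization far more widely than outpatient visits.

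Several stronger readings are tempting, and the article does not support them:

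- **That costs have no power.** The article supports only that none is stated and none can be derived. Likewise, nothing shows that power for total utilization is lower. Sample Size also reports an 80% fall in utilization, and adding event types could move power either way.
- **That the strata prove overdispersion.** They are ranges of observed counts. A single Poisson with mean 3.9 puts about 10%, 35%, 35% and 20% of children in the four strata. The stated reason for stratifying implies some heterogeneity, but not how much.
- **That the SD of 1.8 proves overdispersion.** Two of its three possible readings are compatible with Poisson.
- **That the control rate must be too high.** Table 2 requires only one criterion, and children can qualify on medication step or a challenge test. Some regression to the mean is plausible; its size is unknown. That the pilot had no control group is inferred from the before-after wording and the term quasi-experimental.
- **That follow-up has no slack.** It has little at 36 evaluable children, but reaches about 86% under Poisson if all 40 stay.

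It is also true that a full sensitivity table may belong in the full protocol or analysis plan. Its absence from the article is not the fault; the scope of the printed figure is.

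**Conclusion.** The point holds as a matter of scope and should be corrected. The 97.1% is right for outpatient consultation counts under Poisson variation and the pilot's before and after rates, at 36 evaluable children. It is not power for the primary outcomes as defined. This conclusion rests on the article's own text and needs no outside assumption.

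The loss from the modelling assumptions is less certain because it depends on assumed values. Intervention-period power withstands mild departures (about 93% at k=5, about 87% at a control rate of 1.5) and falls to about 54-73% under the larger ones shown (k=1, a control rate of 1.2, or a 50% true reduction). The follow-up figure is more fragile: about 71% even at k=5. A reader might merge these results into one range, but they belong to different endpoints and different single departures and should stay separate.

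Neither a null cost result nor a null follow-up result should be presented as coming from a well-powered comparison.

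**What to change.** Reword the end of Sample Size to say that:

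1. 97.1% (intervention period) and 80% (follow-up, lasting effect of 80%) apply to outpatient consultation counts, under Poisson variation, with the pilot's before rate for controls and its after rate for eHealth, at 36 evaluable children;
2. no power is claimed for total utilization or for costs;
3. the SD of 1.8 belongs to a named quantity (before count, after count or change).

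Add a short sensitivity statement, here or in the analysis plan, with the intervention period and follow-up reported separately, one departure at a time, and every dispersion, control rate and effect value labelled as assumed. The tables above can serve. Refer to it when interpreting a null result.

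The cost is a paragraph and a less favourable power statement. Sample size, design and data collection do not change.
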